#### Sample size

In order to calculate a sample size, the results from similar researches will be used. Considering pain reduction of 1.5 units, variance of 1.8 with CI 95% and 80% power, and 10% dropouts, 135 participants were estimated to be suitable for this study.

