### Assignment of interventions: allocation

#### Sequence generation

Eligible subjects will be randomly assigned to three groups by block-randomized allocation method with 6 blocks. A randomization will be made by using a website program (http:// random.org). The table will be managed by an individual who is not included in the research team of the trial.

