### Statistical analysis

The comparison of the mean pain intensity of the three groups will be done using repeated measurement, and ANOVA in three different time intervals of before intervention, after the first intervention, and after the second intervention with repeated measures will be used to compare the mean scores of menstrual pain intensity between the groups at different time points. *P* value of less than 0.05 will be considered significant. The statistical analysis will be performed using SPSS version 22.

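### The total of 135 does not follow from the printed sample-size inputs, which give about 45 to 48 participants, or 78 to 81 if 1.8 is a standard deviation

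*Protocol article*

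**What the plan says.** The Sample size section of the protocol article gives, in one sentence, an effect, a measure of spread, a confidence level, a power, a dropout allowance and a result: "Considering pain reduction of 1.5 units, variance of 1.8 with CI 95% and 80% power, and 10% dropouts, 135 participants were estimated". It says that similar studies supplied the basis. It names no formula or test, does not say whether the test is one- or two-sided, and gives no adjustment for multiple comparisons and no correlation between repeated measurements.

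The Sequence generation section gives the number of arms: "Eligible subjects will be randomly assigned to three groups by block-randomized allocation method with 6 blocks". It states no allocation ratio; equal allocation would put 45 in each arm.

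The Statistical analysis section describes the planned comparison: "The comparison of the mean pain intensity of the three groups will be done using repeated measurement". It covers three time points (before treatment and after each of the two treated cycles) and uses a 0.05 significance level. It does not say which contrast the sample size was meant to power.

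**The concern.** A difference of 1.5 against a variance of 1.8 is more than one SD (1.5/1.342 = 1.12). Two-group comparisons of effects that large need roughly a dozen people per arm, not 45. The printed total is about three times what the printed inputs call for. Rounding, the choice between normal and t methods, and the dropout convention cannot close a gap of that size.

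This is the article's only power statement, and it concerns the primary outcome. If effect, spread, power and total cannot all be true together, a reader cannot tell what difference the trial was sized to detect. Nor can the reader tell whether 1.5 is a difference between arms or a before-after change within an arm.

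**Working it through.** **Inputs from the article:** effect 1.5; variance 1.8; 95% confidence; 80% power; 10% dropout; three arms.

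**Assumptions, because the article is silent:** two-sided test; equal arms; 1.5 is a between-arm difference; dropout is applied as n/0.9 per arm.

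**Attempt to reproduce 135.** The normal-approximation size per arm is

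n = 2 (z₁₋α/₂ + z₁₋β)² σ² / δ²

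with (1.960 + 0.842)² = 7.849 at α = 0.05, and (2.394 + 0.842)² = 10.47 at α = 0.05/3.

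- Variance 1.8: 2 × 7.849 × 1.8 / 2.25 = 12.56, so 13. Then 13/0.9 = 14.4, so 15, and 3 × 15 = **45**. The t-based figures are 14, 16 and **48**.
- SD 1.8 (variance 3.24): 2 × 7.849 × 3.24 / 2.25 = 22.6, so 23. Then 23/0.9 = 25.6, so 26, and 3 × 26 = **78**. The t-based figures are 24, 27 and **81**.
- Variance 1.8, Bonferroni for three comparisons: 16.75, so 17, then 19, total **57** (t-based 19, 22, **66**).
- SD 1.8, Bonferroni for three comparisons: 30.15, so 31, then 35, total **105** (t-based 32, 36, **108**).

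**Other standard variants at 80% power with dropout:**

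| Variant | Variance 1.8 | SD 1.8 |
|---|---|---|
| One-sided 5% | 34–39 | 60–66 |
| Three-group one-way ANOVA | 44–57 | 74–99 |
| Many-to-one factor √2 | 60 | 108 |

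None of these gives 135.

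**Readings that need an unstated input.** If the outcome is change from baseline, the variance becomes 2σ²(1 − r), where r is the before-after correlation. The article gives no r. Normal-approximation totals with dropout are:

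- SD 1.8, r = 0: variance 6.48, n = 45.2, so 46, then 52, total 156.
- SD 1.8, r = 0.10: total 138. With r = 0.15: total 132.
- SD 1.8, r = 0.35, Bonferroni for three comparisons: total 135.
- Variance 1.8, r = 0: variance 3.6, total 87; with Bonferroni, 114.

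So 135 can be reached, but only by choosing a correlation, and sometimes an alpha split, that the article does not print.

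**What 135 delivers.** 45 × 0.9 = 40.5, so about 40 evaluable per arm. Power is from the two-sample t test at two-sided 0.05.

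- Variance 1.8: standard error √(2 × 1.8/40) = 0.300; 1.5/0.300 = 5.0; power 99.9%. Difference detectable at 80% power: 0.85.
- SD 1.8: standard error √(2 × 3.24/40) = 0.402; 1.5/0.402 = 3.73; power 96% (90% at α = 0.05/3). Difference detectable at 80% power: 1.14.

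**Working backwards.** The SD for which 40 per arm gives 80% power at 1.5 is 1.5 × √20 / 2.802 = 2.39 (2.36 by t), a variance of about 5.6 to 5.7. No such figure appears in the article.

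**The case against.** The strongest defence is that the endpoint-score comparison may not be what was powered. The article speaks of a pain reduction, its objectives compare pain before and after treatment among the three groups, and its analysis includes the baseline measurement. A change-score calculation is therefore a natural reading, and with SD 1.8 its totals run both above and below 135. This stands, so a reader who infers that no calculation could give 135 goes too far. It does not rescue the printed sentence: it requires 1.8 to be an SD although the text calls it a variance, and it requires a correlation that is not given. Bonferroni with SD 1.8 and 90% power also lands at 130 to 138, but the article states 80%.

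A second defence is that an article condenses a fuller protocol, which may hold the formula and the correlation. That would excuse missing inputs. It does not excuse printed inputs that disagree with the printed result.

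A third is that the discrepancy runs in the safe direction, and on the direct readings that is right.

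It is also tempting to explain 135 as 45 × 3, with a three-arm total mistaken for an arm size. Any equal three-way split of 135 is 45 × 3. A different route, the two-arm total 2 × 22.6 ≈ 45 under SD 1.8, fits equally well. Neither is documented, so the origin remains unknown.

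**Conclusion.** The point holds as a mismatch between stated figures: as printed, 135 is nearly three times the 45 to 48 that the inputs support, and it still exceeds the 105 to 108 reached with SD 1.8 and Bonferroni. This rests on a two-sided test, equal arms and a between-arm difference of 1.5.

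A reader might infer from a wrong 80% that the trial is underpowered. The direct readings show the opposite. Power falls below 80% only on readings with unstated inputs: change scores with SD 1.8 and zero correlation would give about 74% with 40 per arm, and nothing in the article establishes that reading.

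A reader might also infer that the results could not be interpreted. That is too strong, because interpretation will rest on the observed difference and its confidence interval. What is lost is a reliable statement of the difference the trial was designed to detect. This is a correction to a stated figure, not a reason to change the trial's size.

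**What to change.** Keep enrolment at 135 and correct the Sample size paragraph.

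1. State the inputs actually used: whether 1.8 is an SD or a variance; whether 1.5 is a between-arm difference or a before-after change; which comparison was powered; and any alpha adjustment or before-after correlation. The article does not identify 1.5 as the *Rosa foetida* minus placebo difference, so the authors must say what it is.
2. If those inputs reproduce 135, print them with the formula.
3. If they do not, replace the 80% statement with the power, or the detectable difference, that 45 randomised and about 40 evaluable per arm deliver. If 1.8 proves to be an SD and 1.5 an unadjusted between-arm difference, for example, that is about 96% power for 1.5, or 80% power for 1.14.

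The cost is one rewritten paragraph. Recruitment, allocation and treatment are unaffected.

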### Statistical analysis

The comparison of the mean pain intensity of the three groups will be done using repeated measurement, and ANOVA in three different time intervals of before intervention, after the first intervention, and after the second intervention with repeated measures will be used to compare the mean scores of menstrual pain intensity between the groups at different time points. *P* value of less than 0.05 will be considered significant. The statistical analysis will be performed using SPSS version 22.

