**Methods/design:**

A randomized clinical trial will be performed on single students, aged 18 to 24 years. The research samples will be divided into three groups. The students will receive self-care behavior education on dysmenorrhea. Following the education, two of the groups will receive *Rosa foetida* extract capsules and placebo capsules in two consecutive cycles every 8 h for two successive days, respectively. The capsules will have similar physical appearance. The third group will not receive any medication. Data will be collected through demographic characteristic questionnaire, visual analog scale, dysmenorrhea self-care behaviors scale questionnaire, pictorial chart, and menstrual distress scale questionnaire. In order to determine and compare the effect of pharmacological and educational interventions on the severity of dysmenorrhea in groups, an ANOVA analysis of variance test with repeated measures will be used by SPSS software version 22.

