## Methods

### Objectives

Our objectives are (1) to compare the severity of menstrual pain before and after intervention among three groups (*Rosa foetida*, placebo, and self-care); (2) to compare menstrual distress before and after intervention among three groups; and (3) to compare menstrual bleeding severity before and after intervention among three groups.

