#### Dysmenorrhea self-care education

The training program will be held in four sessions for all the eligible participants in the study. The first and second sessions of the educational content will include anatomy and physiology of menstruation, and the third and fourth sessions of the educational content will include exercise and nutrition.

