### Interventions

Group A will receive capsules with 200 mg of *Rosa foetida* extract to be taken three times a day during menstruation days, in addition to self-care instructions. Group B will received capsules with 200 mg of starch (as the placebo group), in addition to self-care instructions. Group C will receive only self-care instructions.

An assistant will code the capsules and seal them in an envelope; then, the envelopes will be given to the researcher to pass to the participants. Each participant will fill out the Pain VAS, Menstrual Distress Questionnaire (MDQ), and Dysmenorrhea Self-Care Scale (DSCS), as well as the pictorial chart in a menstrual cycle before intervention.

Intervention will be done on the first 2 days of two consecutive cycles, and the participants will be requested to take a capsule and then record their pain on the VAS, 1, 2, 4, 8, 12, 24, and 48 h after the start of intervention. In addition to that, the participants will be requested to fill out the MDQ and DSCS at the end of the second day of interventions.

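### The only pain analysis described is a three-group test that includes the no-capsule arm; no extract-versus-placebo contrast is named, and no between-group contrast can show an education effect

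*Protocol article*

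**What the plan says.** All references are to the protocol article.

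- **Statistical analysis:** "The comparison of the mean pain intensity of the three groups will be done using repeated measurement". The ANOVA covers "three different time intervals of before intervention, after the first intervention, and after the second intervention", and a P "value of less than 0.05 will be considered significant". No other analysis of pain is described.
- **Objectives:** the first objective is "to compare the severity of menstrual pain before and after intervention among three groups". No pair of groups is singled out.
- **Interventions:** Group A takes extract capsules, Group B starch capsules, and "Group C will receive only self-care instructions".
- **Dysmenorrhea self-care education:** "The training program will be held in four sessions for all the eligible participants in the study".
- **Abstract, Methods/design:** the purpose of the ANOVA is introduced with "In order to determine and compare the effect of pharmacological and educational interventions on the severity of dysmenorrhea in groups".
- **Sample size:** "Considering pain reduction of 1.5 units" is the planning difference. The section does not say which two arms it separates.
- **Background, last paragraph:** a comparison with placebo is worded, but only for the secondary aims (bleeding and distress) and with no test attached.

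**The concern.** The main objective is the effect of the extract. Education is common to all arms, so only Group A against Group B isolates the extract. Group C takes nothing, its participants know that, and pain is self-reported. A placebo response shared by A and B would separate both from C even if the extract did nothing, and a three-group test responds to that separation. The article gives grounds to expect such a response, because its Background lists placebos among the methods it calls effective.

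The education statement is a separate mismatch. The Abstract says the ANOVA will determine the effect of education, but no randomised arm goes without it.

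At stake is what the headline P value means. As written, it answers whether the three groups differ somewhere. It does not answer whether the extract beats placebo.

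**Working it through.** **Inputs from the article.** Total 135, three groups, 10% dropout, difference 1.5 units, alpha 0.05, and three occasions (one before and two after intervention). The spread is worded as a variance of 1.8.

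**Assumed inputs.** Allocation 1:1:1; two-sided tests; SD 1.8 as the main case, with the literal reading SD = √1.8 = 1.34 also shown; equal correlation ρ of 0.3 to 0.7 between occasions; Group C worse than both capsule groups by d = 0.5, 1.0 or 1.5 units on the two treated occasions; extract exactly equal to placebo.

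**The plan's own figure.** Per arm, n = 2(1.96 + 0.84)²·SD²/1.5².
- SD 1.8: 22.6, so 23; with dropout 23/0.9, so 26; total 78.
- Variance 1.8: 12.6, so 13; with dropout 15; total 45.

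Neither gives 135. That is a separate matter. Here 135 is taken as given: 45 per arm, and 45 × 0.9 = 40.5, so about 40 evaluable.

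**Group main effect** (df 2 and 117). Averaged over three occasions, C is shifted by 2d/3. The variance of a person's mean is SD²(1 + 2ρ)/3.

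λ = n·(2/3)·(2d/3)² / [SD²(1 + 2ρ)/3]

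With n = 40, d = 1.0 and SD 1.8, the numerator is 40 × 0.667 × 0.444 = 11.85.

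| ρ | Denominator | λ | P(significant) |
|---|---|---|---|
| 0.3 | 1.728 | 6.86 | 63% |
| 0.5 | 2.160 | 5.49 | 53% |
| 0.7 | 2.592 | 4.57 | 46% |

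**Group-by-time effect** (df 4 and 234).

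λ = n·(2/3)·(2/3)·d² / [SD²(1 − ρ)], numerator 17.78.

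| ρ | Denominator | λ | P(significant) |
|---|---|---|---|
| 0.3 | 2.268 | 7.84 | 58% |
| 0.5 | 1.620 | 10.97 | 75% |
| 0.7 | 0.972 | 18.29 | 94% |

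Simulation of the same repeated-measures ANOVA gives 46 to 64% and 57 to 93%, which agrees to about one percentage point.

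**Other cases, by the same formulas.**

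| Spread | d | Group effect | Group-by-time |
|---|---|---|---|
| SD 1.8 | 0.5 | 14–19% | 17–36% |
| SD 1.8 | 1.5 | 82–95% | 93–100% |
| Variance 1.8 | 1.0 | 72–88% | 86–100% |

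**Direct A versus B in the same data.** The true difference is zero, so the test rejects at its nominal level. Simulation gives 4 to 5.5%.

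**Power if A versus B is made primary** (40 per arm, difference 1.5).
- SD 1.8: SE = 1.8·√(2/40) = 0.4025; 1.5/0.4025 = 3.73; power = Φ(3.73 − 1.96) = 96%. The smallest difference detectable with 80% power is 2.80 × 0.4025 = 1.13 units.
- Variance 1.8: SE = √(2 × 1.8/40) = 0.30; 1.5/0.30 = 5.0; power 99.9%.

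**Education.** A has education plus extract, B education plus starch, and C education alone. The education term cancels from A − B, A − C and B − C. Only before-after change is left, and that has no control group.

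**The case against.** The strongest reply is that a significant three-group test in this scenario is not a false positive, because Group C really does differ. It becomes a false claim about the extract only if someone reads it that way. A reader might infer that placebo response alone would make the trial positive. The article does not say so: no section makes a significant three-group result the criterion for an extract effect, and the Discussion makes its recommendation depend on a positive effect of Rosa foetida. The Background's placebo wording for bleeding and distress also suggests that placebo is the intended comparator. This stands, and it limits the point to what the planned test can show.

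A reader might also infer an inflated error rate from three unadjusted pairwise tests. The article plans no such tests. Follow-up procedures are commonly left to an analysis plan, and with three groups, pairwise tests made only after a significant overall test need not inflate the error. No multiplicity charge is made here.

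Thirdly, a reader might add regression to the mean, because entry requires a VAS of 5 or more. That would affect only a before-after reading and not the randomised contrasts. The entry VAS and the VAS recorded in the cycle before intervention may also be separate measurements, so its size cannot be fixed from the article.

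Finally, the education claim rests on one phrase in the Abstract, and the aims speak of the extract along with self-care. That makes it a wording correction and not a design failure. The phrase still attributes to the ANOVA something it cannot deliver.

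**Conclusion.** The point holds in limited form. The objective, test and threshold printed for pain all refer to three groups, one of them unblinded by design, and no extract-versus-placebo contrast is named for the primary outcome. A significant result on the described test would not show an extract effect.

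The size depends on a placebo response that the article does not quantify. At 1.0 unit the figures are those derived above for SD 1.8, and they are higher if the variance is literally 1.8. At 0.5 unit they are much smaller. That Group C is open is inferred from its receiving no capsule.

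An unseen analysis plan could add an A-versus-B test, but no analysis can make education estimable between these arms. Because the randomised placebo arm already exists and the remedy is wording, this is a should-fix.

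**What to change.** 1. In Statistical analysis, name A versus B on pain over the treated cycles as the single primary comparison, two-sided 5%.
2. Make A versus C and B versus C secondary, and label them open-label.
3. In the objectives, state the aim as the effect of the extract over placebo when both are added to self-care education.
4. In the Abstract, remove the statement that the analysis determines the effect of education.
5. In Sample size, say that the 1.5-unit difference refers to A versus B.

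The cost is wording, with no extra participants on the article's own planning difference. The price is that A versus C and B versus C lose stand-alone confirmatory status. Trial status says recruitment is under way, so the change should be recorded before any data are compared by arm.

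### Entering the pre-treatment pain score as an outcome level of the repeated-measures ANOVA, not as a covariate, costs precision whichever term of the model is read

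*Protocol article*

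**What the plan says.** The Statistical analysis section of the protocol article names one model for pain, the primary outcome: an "ANOVA in three different time intervals of before intervention, after the first intervention, and after the second intervention with repeated measures". Its purpose is "to compare the mean scores of menstrual pain intensity between the groups at different time points", and a P "value of less than 0.05 will be considered significant".

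The Interventions section shows that the first of the three levels precedes any capsule. The pain VAS and the other scales are completed, "as well as the pictorial chart in a menstrual cycle before intervention". The first objective is "to compare the severity of menstrual pain before and after intervention among three groups".

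The Sample size section gives the planning figures: "Considering pain reduction of 1.5 units" and "variance of 1.8 with CI 95% and 80% power", with 10% dropout and 135 participants. No section uses the pre-treatment score as a covariate.

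**The concern.** Randomisation makes the arms equal in expectation before treatment, so the pre-treatment score carries no treatment effect. Its value lies in explaining differences between women in the treated cycles. Used as a covariate, it removes that variation. Used as a third outcome level, it does so poorly or not at all.

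A repeated-measures ANOVA on three levels yields two tests that could answer the primary question:

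- The group main effect averages over all three levels, including the one where no difference can be expected.
- The group-by-time interaction compares changes. In effect it subtracts the whole baseline score, when only the part that predicts the later score should be removed.

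At stake are the width of the confidence interval for the primary comparison and the chance of missing an effect smaller than the planned 1.5 units.

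**Working it through.** **Inputs from the documents.** Difference 1.5 units; 1.8 as variability; 80% power; 10% dropout; N = 135; significance level 0.05; three groups; one pre-treatment and two treated cycles.

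**Assumptions.** Equal allocation, so 135/3 = 45 per arm and 45 × 0.9 = 40.5, taken as 40 evaluable. Two-sided test. One pain score per cycle, with equal variance σ² and one common correlation ρ between cycles. The article gives no ρ; 0.3, 0.5 and 0.7 are shown. The same true difference d holds in both treated cycles.

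**Step 1: the plan's own figure.** With n = 2σ²(1.96 + 0.84)²/d² per arm:

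- Variance 1.8: 2 × 1.8 × 7.85/2.25 = 12.6, so 13 per arm, 15 with dropout, 45 in total.
- SD 1.8: 2 × 3.24 × 7.85/2.25 = 22.6, so 23 per arm, 26 with dropout, 78 in total.

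Neither gives 135, so the article does not settle which reading of 1.8 was meant. Both are carried forward, with 135 taken as fixed.

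**Step 2: one formula for all analyses.** Let P be a woman's mean over the two treated cycles and B her pre-treatment score. Each analysis compares arms on P − bB, which has expected difference d and variance σ²[(1+ρ)/2 − 2bρ + b²].

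- Group main effect: (2P + B)/3 is two thirds of P + B/2, so b = −1/2. The reported difference is 2d/3; 1.5 becomes 1.0.
- Post-minus-pre contrast: b = 1.
- Baseline-adjusted (ANCOVA): b is the fitted slope, here b = ρ, which minimises the variance.

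| Variance of P − bB, in σ² | ρ = 0.3 | ρ = 0.5 | ρ = 0.7 |
|---|---|---|---|
| Main effect, 0.75(1+2ρ) | 1.20 | 1.50 | 1.80 |
| Change, (1+ρ)/2 + 1 − 2ρ | 1.05 | 0.75 | 0.45 |
| ANCOVA, (1+ρ)/2 − ρ² | 0.56 | 0.50 | 0.36 |
| Efficiency, main effect vs ANCOVA | 47% | 33% | 20% |
| Efficiency, change vs ANCOVA | 53% | 67% | 80% |

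An interval for the change contrast is therefore wider than the adjusted one by √(1/0.533) = 1.37, √1.5 = 1.22 and √1.25 = 1.12 times.

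**Step 3: power.** Pairwise comparison, non-central t, 40 per arm, two-sided 0.05, at ρ = 0.3/0.5/0.7:

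| True d | SD | Main effect | Change contrast | ANCOVA |
|---|---|---|---|---|
| 1.5 (planned) | 1.8 | 92/85/78% | 95/99/>99% | >99% |
| 1.5 (planned) | 1.34 | 99.5/98/96% | >99% | >99% |
| 1.0 (assumed) | 1.8 | 61/52/45% | 67/81/96% | 91/93/98% |
| 1.0 (assumed) | 1.34 | 85/77/69% | 89/97/99.8% | >99% |

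The change column is a two-arm contrast with one degree of freedom. The interaction over three groups and three times is a 4-df test that also picks up differences between the two treated cycles. With SD 1.8 and d = 1.0 in the Rosa foetida arm only, its power is 59/75/94%.

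**The case against.** The best defence is that the planned model is conventional and valid, and adequate for what it was designed to detect. The stated purpose ("to compare the mean scores of menstrual pain intensity between the groups at different time points") and the before-and-after objective lean towards the group-by-time term, where no dilution occurs. On that reading, power for the pairwise change contrast at 1.5 units is 95% or more even with SD 1.8. Which term decides may also be settled in an analysis plan that is not shown, so the article's silence on it is no fault in itself.

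All of this stands, and it limits the point. It does not remove it, because the loss occurs under either term. The group main effect gives the baseline the wrong sign and the change contrast gives it too much weight.

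A reader might infer more than the documents support:

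- **That the treatment effect will be reported as two thirds of its size.** This follows only if the time-averaged group effect decides, and nothing says it does.
- **That the analysis is biased or inflates false positives.** It is not and does not. The time-averaged difference is a different contrast, smaller than the treated-cycle effect, and its test is valid under the null.
- **That the trial is underpowered.** The figures near 50% need a true effect of 1.0, which the article does not mention, together with 1.8 read as an SD and the main effect as the deciding test.

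**Conclusion.** The point holds as a recommendation about efficiency. The stated model uses the pre-treatment VAS less well than baseline adjustment does: relative efficiency is 47/33/20% for the group main effect and 53/67/80% for the change contrast at ρ = 0.3/0.5/0.7.

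The direction does not depend on the reading of 1.8 or on the size of the effect. Under equal variances, ANCOVA is the more efficient for any correlation from 0 to below 1; only the amount depends on ρ, which is assumed. At the planned 1.5 units, power stays at about 78% or higher over these correlations, so the trial's validity is not in question. The practical cost is a wider interval for the primary comparison, and a real loss of power if the extract's advantage over placebo is smaller than planned. That is conceivable, since every arm also receives the self-care education.

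**What to change.** For pain, treat only the two treated cycles as outcomes and enter baseline VAS as a covariate. Either of these will do:

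- ANCOVA on the mean of the two cycles, with group and baseline VAS; or
- SPSS MIXED with group, cycle, group-by-cycle and baseline VAS, with cycles correlated within participant.

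State that the primary result is the baseline-adjusted Rosa foetida minus placebo difference over the two treated cycles, with its 95% CI. Comparisons with the self-care group can come from the same model.

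Use the same approach for a secondary outcome that has both a baseline and a post-treatment score. The MDQ qualifies according to the Interventions section. That section lists the pictorial chart only before treatment, so its post-treatment collection should be confirmed first.

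The cost is a change of wording, made before the data are analysed. Baseline VAS is already collected and SPSS 22 fits both models. No added participants, visits or measurements are needed.
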